## Objectives

2

The primary objective of this study is to evaluate the effectiveness of the suggested level of care made by the AI compared to the healthcare team and the effectiveness of the stratified care model. This will be assessed using the change in the severity of depressive symptoms using the Patient Health Questionnaire – 9 Item (PHQ-9) (35) and Quick Inventory of Depressive Symptoms (QIDS) (36) scores, and the quality of life and functioning using Assessment of Quality of Life (AQoL-8D) (37) scores between the start and the end of the 13-session e-CBT program.

The secondary objectives include evaluating compliance and treatment completion using the number of sessions completed by each participant and evaluating the time and cost commitment of initial assessments (i.e., manual participant stratification by the healthcare team vs. the AI) and the different care intensities (i.e., only e-CBT, e-CBT + phone calls, or e-CBT + video calls). We will also evaluate the functional consequence of our interventions on participant quality of life via Quality-adjusted life years (QALY)s (38). Throughout the study, QALY estimates will be derived from AQoL-8D scores using the area under the curve method (39, 40). Outlined below are the research questions and the corresponding study hypotheses:

1 Will participants with major depressive disorder (MDD) assigned to an e-CBT program by an AI show similar outcomes in depressive symptoms at 3 months to those allocated to an e-CBT program decided by a team of healthcare professionals?

– We hypothesize that the outcomes in depressive symptoms of treatment arm 1 will be comparable to the outcomes of treatment arms 2 and 3 following e-CBT treatment.

2 How does AI-based clinical decision-making compare to that of a multi-professional healthcare team when allocating individuals with depression to an e-CBT program with different degrees of care intensity?

– We hypothesize that AI-based clinical decision-making (treatment arm 2) will provide suggestions comparable to that of a multi-professional care team (treatment arm 1).

3 Is this novel AI approach to e-CBT time and cost-efficient and comparable to the standard multi-professional healthcare decision-making team?

– We hypothesize that the AI approach will decrease the overall time and cost commitment of providing e-CBT.

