### Sample size determination

3.10

In our previous clinical trials and gathered data (47), the average PHQ-9 score changed from 16.2 before e-CBT to 11.48 after 12 sessions of e-CBT (joint standard deviation; SD = 5.45). Based on these numbers, the effect size (Hedges’ G) is equal to 0.86. Given the effect size and a power of 0.8, we would need 14 participants to observe a significant effect in a paired sample *t*-test. Considering the completion rate of 45%, we would require 31 participants in each group to observe significant results. Given the two treatment arms and three treatment intensities, we would require 186 participants to detect significant clinical change across all groups. We believe this sample size is large enough to perform further analyses on factors such as the role of sex and gender in treatment efficacy and completion rate.

To follow up on this sample size determination, we will use previously collected data as mentioned above to simulate the population and use a random sampling method to determine the effect size for our power calculation. We will do this by simulating a population based on the mean and standard deviation of our previous e-CBT studies and collecting data, then randomly sampling participants to each treatment arm. This simulation will be developed using Python code. Based on this random sampling, we will calculate the effect size, set the power of 0.8, and consider the completion rate of 45% to determine the sample size required to detect a significant clinical change across the groups.

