## Statistical analysis

4

Initially, all data will be examined for missing, nonsensical, and outlying variables. Missing data will not be attributed and will be treated as missing. All statistical analyses will be performed at the end of the trial and will consider a significance level of 0.05 and 95% confidence intervals. Analyses will be conducted to account for and assess differences across sex and gender identifications, and how these factors affect the adaptability and efficacy of e-CBT.

### Hypothesis 1: outcomes in depressive symptoms of treatment arm 1 will be comparable to treatment arms 2 and 3

4.1

Clinical outcomes of the healthcare teams’ decision (arm 1) versus the AI’s decision (arm 2), will be compared by assessing the treatment completion rate, number of completed sessions, and change in questionnaire scores. The completion rate across the two study arms and three levels of care will be calculated using a 2 × 3 × 2 contingency matrix (i.e., healthcare team vs. AI × 3 different treatment intensities × completers vs. dropouts) and chi-square analysis to compare within and between completion rates in the two arms. We will use a 2 × 3 (i.e., healthcare team vs. AI × 3 different levels of care) two-way analysis of variance (ANOVA) to compare the number of completed sessions across participant groups and care levels. Questionnaires are collected at 3 different times; at the start (for all participants), midway (for those who completed at least 6 sessions), and end of the study (for those who completed the treatment program). We will use a 2 × 3 × 3 (i.e., healthcare team vs. AI × 3 different levels of care × 3 time points) linear mixed-effects model for each questionnaire to compare clinical outcomes within and between groups and times. A mixed-effects model analysis will account for any missing data caused by participant dropout. Finally, we will assess if demographic covariables affect clinical outcomes using multiple 2 × 2 × 3 × 3 (demographic factors (e.g., male vs. female) × healthcare team vs. AI × 3 different levels of care × 3-time points for the questionnaire’s score) mixed-effects model to account for each demographic variable (i.e., sex, gender, age, and income). Bonferroni corrections will follow the ANOVA analyses in *post hoc* analyses.

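### The 186 participants are sized for a before-after PHQ-9 change within each of six cells, so the stated 0.8 power does not cover the randomised AI-versus-team comparison

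*Protocol article*

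**What the plan says.** Section 2 (Objectives) gives the primary objective two parts. The first is to "evaluate the effectiveness of the suggested level of care made by the AI compared to the healthcare team"; the second is the effectiveness of the stratified care model. Both are assessed by change in PHQ-9, QIDS and AQoL-8D from start to end of the programme. The first research question asks whether AI-allocated participants will "show similar outcomes in depressive symptoms at 3 months to those allocated to an e-CBT program decided by a team of healthcare professionals", which is a question of comparability.

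Section 3.3 randomises 93 participants to each arm. Section 4.1 compares the arms on change in questionnaire scores with an arm by intensity by time mixed model. Section 4 adds that the analyses "will consider a significance level of 0.05 and 95% confidence intervals".

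Section 3.10 starts from earlier data in which "the average PHQ-9 score changed from 16.2 before e-CBT to 11.48 after 12 sessions of e-CBT" ("joint standard deviation; SD = 5.45"), an effect size of 0.86. It continues: "Given the effect size and a power of 0.8, we would need 14 participants to observe a significant effect in a paired sample" t-test. Allowing for 45% completion gives 31 per group, and then: "Given the two treatment arms and three treatment intensities, we would require 186 participants to detect significant clinical change across all groups". A follow-up simulation is planned. It would build a population from the mean and SD of earlier e-CBT studies, "then randomly sampling participants to each treatment arm", and recompute the sample size.

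**The concern.** The calculation answers whether PHQ-9 falls from before to after treatment inside one cell. Natural recovery or regression to the mean can produce such a fall whoever chose the care level, so power for that test says nothing about whether AI and team allocation give similar results.

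The gap matters more because the hypothesis is comparability. If the arms are compared imprecisely and no margin is set, a non-significant difference could be taken as support for the hypothesis when the interval still allows a difference that matters. The plan gives the reader no figure for how precise the randomised comparison will be.

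**Working it through.** **1. The plan's own figure.** Inputs from section 3.10: means 16.2 and 11.48, SD 5.45, power 0.8, completion 45%. Alpha 0.05 is from section 4; sidedness is not stated, and two-sided is assumed.
- Effect size: (16.2 − 11.48)/5.45 = 4.72/5.45 = 0.866 (stated 0.86).
- Paired t-test, d = 0.86: n = 12.7, so 13 (power 0.812); at the stated 14, power is 0.844.
- 14/0.45 = 31.1, taken as 31 (rounding up would give 32); 31 × 6 = 186.

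The 186 is therefore reproduced, apart from immaterial rounding. Every input is within-group. No between-arm difference, two-sample test or margin enters, and the 0.8 belongs to one before-after test in one cell.

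**2. What 93 per arm gives for AI versus team.** Assumption: SD 5.45, described as a joint SD, also applies to the between-arm outcome. At 45% completion, 93 × 0.45 = 41.85, about 42 completers per arm. Section 4.1 collects end-of-study scores from those who completed the programme.
- Standard error = 5.45 × √(2/n): 1.189 at n = 42; 0.799 at n = 93.
- 95% CI half-width = t × SE: 1.989 × 1.189 = 2.37; 1.973 × 0.799 = 1.58.
- Detectable difference at 80% power, two-sample t-test: 0.619 × 5.45 = 3.37 points (n = 42); 0.413 × 5.45 = 2.25 points (n = 93). As shares of the 4.72-point pre-post change: 3.37/4.72 = 71% and 2.25/4.72 = 48%.

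| Quantity | 42 per arm | 93 per arm |
|---|---|---|
| Detectable difference, 80% power | 3.37 | 2.25 |
| 95% CI half-width | 2.37 | 1.58 |
| Power for a true 2-point difference | 0.38 | 0.70 |
| Smallest non-inferiority margin, 80% power | 3.33 | 2.24 |

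The last row is SE × (1.960 + 0.842), with one-sided 0.025 and a true difference of zero.

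**3. Sensitivity to the SD.** If change scores are analysed, the SD of change is 5.45 × √(2(1 − r)), where r is the pre-post correlation, which the document does not give. At r = 0.7 it is 4.22 and at r = 0.3 it is 6.45. The detectable difference at 42 per arm is then 0.619 × 4.22 = 2.6 to 0.619 × 6.45 = 4.0 points.

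**4. Enrolment for assumed margins.** With SD 5.45, 45% completion and 80% power on completers, non-inferiority needs 117 completers per arm (520 enrolled in total) at a margin of 2 points, and 52 per arm (232 enrolled) at 3 points. These margins are illustrations only.

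**5. The within-cell basis itself.** Thirty-one per cell is not assured, because the AI or the team assigns intensity. In the 190 earlier participants described in section 3.3.2, the algorithm's split was 62, 100 and 28. The smallest share is 28/190 = 14.74%, so 93 × 0.1474 = 13.7, about 14 enrolled, and 13.7 × 0.45 = 6.2, about 6 completers. Paired power at d = 0.86 with 6 completers is about 0.40. This applies the retrospective AI split to one arm; the team's split is unknown.

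**The case against.** Five points can fairly be made for the plan.

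- **The primary objective is not only between-arm.** It also covers the stratified care model, to which a pre-post calculation has some relevance. That stands, and limits the finding to the AI-versus-team part. Even for the other part, the cell sizes assumed are not assured (step 5).
- **The plan does not claim 0.8 power for AI versus team.** It names a paired test and a clinical change across groups. That stands too. A reader might infer a false power claim for the randomised contrast, but the text supports only that this contrast has no stated power.
- **The simulation may repair the gap.** A reader might go the other way and infer that it fixes the arm difference at zero by drawing both arms from one population. The outline is too short to establish either. It does not say whether an arm or care-level effect is imposed, or which contrast supplies the effect size. What can be said is that it states no between-arm difference or margin.
- **Forty-two per arm is pessimistic.** The planned mixed model uses earlier scores from participants who later drop out, so precision should lie between the two columns. This stands, and is why both are shown.
- **The SD is borrowed.** Using 5.45 for the between-arm outcome is an assumption of this check, not of the plan; hence the range in step 3.

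**Conclusion.** The point holds in this form: the 0.8 power in section 3.10 belongs to a within-cell pre-post test and does not extend to the randomised AI-versus-team comparison, for which the document states neither a difference nor a margin.

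On SD 5.45 and two-sided 0.05, 186 participants give that comparison a detectable difference between 2.25 points (everyone contributes) and 3.37 points (completers only, or about 2.6 to 4.0 over the correlations considered). The non-inferiority margin supportable at 80% power is between about 2.2 and 3.3 points. The between-arm figures are illustrative, because the plan gives no target to hold them against.

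Two further conclusions are tempting, and the document supports neither. One is that 186 is too few; the other is that it can stay as it is. Step 4 shows that the answer turns on the margin. Nor does this make the pre-post calculation irrelevant to the whole primary objective.

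**What to change.** In section 3.10:

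1. State that the 0.8 power refers only to a before-after test within one cell, and delete or limit the sentence claiming detection of clinical change across all groups.
2. Report what 93 per arm gives for the between-arm PHQ-9 contrast (CI half-width, detectable difference, and power over a range of differences or margins) on both the 45%-completer and the all-randomised bases. Mark the SD as an assumption and show a range.
3. In the planned simulation, set the between-arm difference explicitly over a stated range of differences or margins, using the expected care-level mix and dropout in place of equal cells.

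The cost is rewording plus a re-specified run of a simulation already planned. The sponsor must also choose and justify the range of margins, which is more than an edit. The downside is a less favourable stated power. The revised text should not say that no increase in sample size is needed unless a margin is given to support it.

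### Section 3.10 believes 186 is large enough for sex and gender analyses, but that number was sized only for within-group change, and among about 84 expected completers only large sex differences are detectable

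*Protocol article*

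**What the plan says.** Section 3.10 (Sample size determination) starts from earlier data in which "the average PHQ-9 score changed from 16.2 before e-CBT to 11.48 after 12 sessions of e-CBT" ("joint standard deviation; SD = 5.45"), and gives an effect size that "is equal to 0.86". It continues: "Given the effect size and a power of 0.8, we would need 14 participants" for a paired t-test. Then: "Considering the completion rate of 45%, we would require 31 participants in each group". Two arms times three intensities give 186. The paragraph closes with the belief that this number is "large enough to perform further analyses on factors such as the role of sex and gender in treatment efficacy and completion rate". No calculation accompanies that last statement.

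Section 4 (Statistical analysis) commits to the work: "Analyses will be conducted to account for and assess differences across sex and gender identifications". Section 4.1 specifies mixed models that cross each demographic factor with arm, care level and time (2 × 2 × 3 × 3). It also says that midway questionnaires come from those with at least six sessions done, and end questionnaires only from those who finish the programme.

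**The concern.** The calculation in section 3.10 answers one question: whether a single arm-by-intensity group shows a change from before to after treatment. Comparing the sexes is a between-group question, and comparing the arm effect across sexes is an interaction. Neither entered the calculation, so the adequacy statement does not follow from it.

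What is at stake is how a null result is read. If the published plan says the sample is adequate for sex and gender, a non-significant term is easily taken as showing no difference. Section 3.3.2 already words its earlier data in that way: non-significant p-values for sex (0.18 for sessions, 0.46 for PHQ-9 change) are described as the absence of an effect.

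**Working it through.** **Inputs.** From section 3.10: change 16.2 − 11.48 = 4.72 points, SD 5.45, power 0.8, completion 45%, total 186. From section 3.3: 93 per arm. From section 4: the analyses "will consider a significance level of 0.05 and 95% confidence intervals"; I take the test as two-sided. Assumed: a sex split from 50:50 (the most favourable) to 30:70, the same in both arms, and 5.45 as the SD of the change, which is how the plan's paired test uses it.

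**The plan's own figure.** 4.72/5.45 = 0.866, given as 0.86. Exact power of the paired t-test at 0.86 is 0.812 with 13 and 0.845 with 14 participants. Then 14/0.45 = 31.1, given as 31, and 31 × 6 = 186. The chain reproduces. Expected completers: 0.45 × 186 = 83.7, about 84.

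**Formulas.** For N people with end scores and a fraction p of one sex:

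- Sex main effect on change, pooled over arms: SE = SD × √(1/(Np) + 1/(N(1 − p))).
- Sex by arm (difference of two differences, equal arms): SE is twice the main-effect SE.
- Detectable difference at 80% power = (1.960 + 0.842) × SE = 2.80 × SE.

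Example, 84 completers at 50:50: SE = 5.45 × √(1/42 + 1/42) = 1.19, so the main effect is 2.80 × 1.19 = 3.33. For sex by arm, SE = 2.38 and the result is 6.66.

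| PHQ-9 contrast | People with end scores | Detectable, 50:50 | Detectable, 30:70 | As % of 4.72 | Power for 2.36 points (half of 4.72) |
|---|---|---|---|---|---|
| Sex main effect | 84 | 3.33 | 3.64 | 71 to 77 | 0.51 to 0.44 |
| Sex by arm | 84 | 6.66 | 7.27 | 141 to 154 | 0.17 to 0.15 |
| Sex main effect | 186 | 2.24 | 2.44 | 47 to 52 | 0.84 to 0.77 |
| Sex by arm | 186 | 4.48 | 4.89 | 95 to 104 | 0.31 to 0.27 |

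The 84 rows follow the plan's completion rate and its completer-only end questionnaire. The 186 rows are an upper bound with no dropout. The mixed model also uses midway scores from some non-completers, so it lies between the two.

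**Sensitivity to the SD.** All PHQ-9 figures scale in proportion to the SD. If 5.45 is the SD of single scores with pre-post correlation r, the SD of change is 5.45 × √(2(1 − r)), which equals 5.45 at r = 0.5. The sex-by-arm figure for 84 completers at 50:50 falls to 4.72 only when the SD of change is 3.86, that is, r about 0.75.

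**Completion.** All 186 count here. SD = √(0.45 × 0.55) = 0.497. Main effect: 2.80 × 0.497 × √(1/93 + 1/93) = 0.20 at 50:50, and 0.22 at 30:70 (55.8 and 130.2 people). Sex by arm is twice that before rounding: 0.41 and 0.45. So about 20 to 22 and 41 to 45 percentage points.

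**The case against.** The strongest defence is that the sentence need not mean sex by arm. The role of sex in efficacy can mean simply whether men and women change by different amounts on e-CBT, pooled over arms, which is what section 3.3.2 examined in 190 earlier participants. On that reading the detectable difference stays below 4.72 in every case shown, and with end scores from all 186 and an even split, power for a 2.36-point sex difference is 0.84. This stands, so the two contrasts have to be reported separately. It does not rescue the sentence: section 4.1 also plans the crossed model, and at the plan's own completion rate power for a 2.36-point main effect is only 0.44 to 0.51.

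A reader might infer that the detectable sex-by-arm effect always exceeds the whole e-CBT effect. The documents do not support that: with end scores from all 186 and an even split it is 4.48, just under 4.72. A reader might also halve the 14 completers per group to 7 by sex and quote the low power of a paired test there. No such test is planned; the model in section 4.1 pools across cells.

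The wording is a belief about further analyses, and none of the three hypotheses concerns sex or gender. That limits the weight of the point, but it remains a statement of adequacy. The follow-up simulation in section 3.10 does not fill the gap, since as described it samples people into treatment arms and does not mention sex.

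**Conclusion.** The point holds as a correction of a stated property, not as an error in 14, 31 or 186. The sizing gives no basis for the adequacy claim. Under the plan's SD and completion rate, neither contrast reaches 0.8 power among completers for a difference of half the assumed e-CBT change. Sex by arm falls short of that in every case shown (0.15 to 0.31), and for completion only very large sex-by-arm differences could be seen.

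The figures rest on 5.45 as the SD of change, an assumed sex split of 50:50 to 30:70, two categories, and normal approximations. More than two gender categories, or terms that also involve care level, would be estimated less precisely. Nothing in the article says that a null result will be presented as equal benefit of AI triage across sexes; that is a risk the sentence creates, not something the plan declares.

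**What to change.** Replace the adequacy sentence in section 3.10 with the detectable differences at 80% power, main effect and sex by arm separately, with their assumptions:

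- PHQ-9 change, about 84 completers: about 3.3 to 3.6 points (sex main effect) and 6.7 to 7.3 points (sex by arm).
- PHQ-9 change, end scores from all 186: about 2.2 to 2.4 and 4.5 to 4.9 points.
- Completion, all 186 at a 45% rate: about 20 to 22 and 41 to 45 percentage points.
- Assumptions: SD of change 5.45, sex split 50:50 to 30:70, two-sided 0.05.

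In section 4, label the sex and gender analyses exploratory, report their estimates with 95% confidence intervals, and state that a non-significant result is not evidence of no difference.

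The sample size stays at 186 and the planned model need not change. The cost is a few sentences and a less favourable stated capability.

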## Statistical analysis

4

Initially, all data will be examined for missing, nonsensical, and outlying variables. Missing data will not be attributed and will be treated as missing. All statistical analyses will be performed at the end of the trial and will consider a significance level of 0.05 and 95% confidence intervals. Analyses will be conducted to account for and assess differences across sex and gender identifications, and how these factors affect the adaptability and efficacy of e-CBT.

### Hypothesis 1: outcomes in depressive symptoms of treatment arm 1 will be comparable to treatment arms 2 and 3

4.1

Clinical outcomes of the healthcare teams’ decision (arm 1) versus the AI’s decision (arm 2), will be compared by assessing the treatment completion rate, number of completed sessions, and change in questionnaire scores. The completion rate across the two study arms and three levels of care will be calculated using a 2 × 3 × 2 contingency matrix (i.e., healthcare team vs. AI × 3 different treatment intensities × completers vs. dropouts) and chi-square analysis to compare within and between completion rates in the two arms. We will use a 2 × 3 (i.e., healthcare team vs. AI × 3 different levels of care) two-way analysis of variance (ANOVA) to compare the number of completed sessions across participant groups and care levels. Questionnaires are collected at 3 different times; at the start (for all participants), midway (for those who completed at least 6 sessions), and end of the study (for those who completed the treatment program). We will use a 2 × 3 × 3 (i.e., healthcare team vs. AI × 3 different levels of care × 3 time points) linear mixed-effects model for each questionnaire to compare clinical outcomes within and between groups and times. A mixed-effects model analysis will account for any missing data caused by participant dropout. Finally, we will assess if demographic covariables affect clinical outcomes using multiple 2 × 2 × 3 × 3 (demographic factors (e.g., male vs. female) × healthcare team vs. AI × 3 different levels of care × 3-time points for the questionnaire’s score) mixed-effects model to account for each demographic variable (i.e., sex, gender, age, and income). Bonferroni corrections will follow the ANOVA analyses in *post hoc* analyses.

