### Questionnaires & follow-up

3.9

Participants will complete a series of validated questionnaires at baseline including the Patient Health Questionnaire – 9 Item (PHQ-9), Sheehan Disability Scale (SDS), Quick Inventory of Depressive Symptoms (QIDS), Assessment of Quality of Life (AQoL-8D), and a demographic questionnaire. The PHQ-9 and QIDS questionnaire will be used to assess depressive symptoms and the AQoL-8D questionnaire will assess the participants’ quality of life. These three questionnaires provide insight into the participant’s mental status and perceived quality of life in the context of their depression. Additionally, the SDS will be used to assess the patient’s functional impairment for the clinician group assessment during baseline. During the program, participants will complete the PHQ-9 every 3 weeks (i.e., weeks 4, 7, 10, and 13), and the QIDS and AQoL-8D at weeks 7 and 13. All questionnaires (i.e., PHQ-9, QIDS, and AQoL-8D questionnaires) will be filled at the 3, 6, and 12-month follow-up periods to measure post-study outcomes.

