### Hypothesis 3: the AI approach will decrease the time and cost commitment of providing e-CBT

4.3

The cost of initial assessments (i.e., manual participant stratification by the healthcare team vs. the AI) and the different care intensities (i.e., only e-CBT, e-CBT + calls, or e-CBT + pharmacotherapy) will also be evaluated. These costs will be evaluated from a health sector and societal perspective (38). For this analysis we will use (1) healthcare costs paid by the government of Ontario as well as healthcare utilization costs self-reported by participants using a resource-use questionnaire (39, 40); (2) medical and productivity costs due to work absence, evaluated using the Questionnaire on Healthcare Consumption and Productivity Losses for patients with a Psychiatric Disorder (TiC-P) (49); (3) intervention costs including staff time-commitment to deliver interventions, development and maintenance costs, and time commitment to assess and enroll participants into the online program. The costs will be expressed in Canadian dollars (CAD). We will use a 2 * 3 (i.e., healthcare team vs. AI * 3 different levels of care) two-way ANOVA to compare costs within and between arms.

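### The no-imputation rule is relaxed only for the questionnaire mixed models, so per-person QALYs and any cost total with self-reported parts become complete-case comparisons that condition on staying in the programme.

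*Protocol article*

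**What the plan says.** All places are in the protocol article.

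- **Statistical analysis (section 4), opening paragraph:** "Missing data will not be attributed and will be treated as missing". I read the verb as meaning imputed. The rule carries no exception.
- **Hypothesis 1 (4.1):** a linear mixed-effects model is fitted for each questionnaire, and "A mixed-effects model analysis will account for any missing data caused by participant dropout". Questionnaire scores are taken at the start from everyone, then "midway (for those who completed at least 6 sessions") and at the "end of the study (for those who completed the treatment program").
- **Objectives (section 2):** "QALY estimates will be derived from AQoL-8D scores using the area under the curve method". No model for the resulting QALYs is given.
- **Hypothesis 3 (4.3):** a 2 × 3 "two-way ANOVA to compare costs within and between arms". The inputs include self-reported health-care use, the TiC-P, and staff-side intervention and assessment costs.
- **Questionnaires & follow-up (3.9):** AQoL-8D at baseline and weeks 7 and 13, and then "All questionnaires (i.e., PHQ-9, QIDS, and AQoL-8D questionnaires) will be filled at the 3, 6, and 12-month follow-up periods". This sentence is not limited to completers.
- **Sample size determination (3.10):** "Considering the completion rate of 45%, we would require 31 participants in each group to observe significant results".

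**The concern.** A likelihood-based mixed model can use a participant with some visits missing. An area under the curve computed for each person cannot, unless the missing visit is filled in, and an ANOVA on a total cost needs that total for each person. With filling-in barred, anyone lacking a needed AQoL-8D score or self-reported cost item leaves the comparison.

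Who leaves is not random. Section 4.1 ties the midway and end questionnaires to sessions attended, so a complete record largely means having stayed in treatment. The Introduction says the algorithm sets care intensity from the probability of dropping out, and completion is an outcome in sections 2 and 4.1. Restricting the QALY and total-cost contrasts to complete records therefore conditions on a post-randomisation variable that the randomised factor is meant to move. If one arm keeps more people in treatment, that benefit or cost does not enter these contrasts.

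At stake are the QALY objective and the part of Hypothesis 3 that uses participant reports.

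**Working it through.** **1. The plan's own figures.** Effect size: (16.2 − 11.48)/5.45 = 0.866 (stated 0.86). A paired t-test at two-sided 0.05 and 80% power needs 13 people, or 14 with a small-sample-corrected effect of 0.815 (stated 14). Inflation for completion: 14/0.45 = 31.1 (stated 31). Total: 31 × 2 arms × 3 intensities = 186, or 93 per arm. The chain reproduces closely enough, so 45% is the completion rate the plan works with. The earlier e-CBT-only sample in 3.3.2 agrees: (33 + 41 + 10)/190 = 84/190 = 44%.

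**2. Complete treatment-period records, if questionnaires stop with the programme as 4.1 describes.**

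| Completion | Source | Complete records | Per arm | SE ratio, √(186/complete) |
|---|---|---|---|---|
| 45% | 3.10 | 0.45 × 186 = 83.7, about 84 | about 42 | √(186/83.7) = 1.49 |
| 68% (32% dropout) | Introduction | 0.68 × 186 = 126.5, about 126 | about 63 | √(186/126.5) = 1.21 |

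**3. Detectable difference between arms** (two-sample t-test, two-sided 0.05, 80% power): 0.41 SD with 93 per arm, 0.50 SD with 63 and 0.62 SD with 42. The first figure assumes every record is observed.

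**4. What conditioning on completion removes.** Let r1 and r2 be the completion proportions in the two arms, and let completers gain g1 and dropouts g0, the same in both arms. The difference over all randomised participants is (r2 − r1) × (g1 − g0). The completers-only difference is g1 − g1 = 0. The following values are assumptions, not protocol figures:

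- Over 13 weeks (0.25 year), take utility rising linearly by 0.15 in completers and 0.05 in dropouts, with completion 50% versus 40%. The difference is 0.25 × 0.5 × 0.10 × 0.10 = 0.00125 QALY.
- With QALY gains of 0.05 to 0.10 in completers and 0 to 0.05 in dropouts (plausible only over a longer horizon), and completion 45% versus 55% or 65%, the difference runs from 0.10 × 0.05 = 0.005 to 0.20 × 0.10 = 0.020 QALY.

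**5. Is missingness likely to be related to outcome?** In 3.3.2, completion across the algorithm's three strata was 33/62, 41/100 and 10/28 (53%, 41%, 36%). Final PHQ-9 above 14 was 12/62, 31/100 and 11/28 (19%, 31%, 39%). The strata that completed least did worst. This is a between-stratum pattern; it does not show the relation within a stratum.

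**6. The separate completion test in 4.1.** With 93 per arm, its power is about 27% for 45% versus 55% and 79% for 45% versus 65%.

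**The case against.** The strongest reply is that the plan never says QALYs or costs are complete-case. Section 2 names the area-under-the-curve method without fixing visits, horizon or test, and a QALY built from AQoL-8D mixed-model means would impute nothing and fit the present text. Missing-data methods for a secondary economic outcome are also commonly left to the SAP. The first part stands as a remedy. It does not remove the problem, because the plan does not choose that route. The second fails because the rule is stated, not omitted: an SAP that imputed would contradict it.

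Three stronger readings are tempting, and the documents do not support them.

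- **A reader might infer that 55% of participants are lost from these endpoints.** The 55% is 1 − 0.45, programme non-completion. No missing-data rate is given for AQoL-8D or costs, and 3.9 does not limit the 3-, 6- and 12-month forms to completers. The loss could be smaller, or larger if later forms are missed.
- **A reader might infer that a retention difference is erased from the trial.** Section 4.1 compares completion and sessions completed, both known for everyone randomised.
- **A reader might infer that the whole cost comparison is affected.** Assessment and deliberation time (3.3.1) and staff time for delivery and enrolment (4.3) need no participant form. The call time of someone who stops early is still known. Only self-reported items, and totals containing them, are affected.

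It is also fair that imputation cannot restore the precision of 186 observed records, so the 1.49 ratio measures the cost of missing data, not the gain from changing the rule.

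The resource-use questionnaire and TiC-P do not appear in 3.9. Its baseline list is introduced as non-exhaustive and 4.3 commits to both instruments, so this is a scheduling point to reconcile, not evidence that they will go uncollected.

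**Conclusion.** The point holds in limited form and should be corrected. Read literally, section 4 makes the per-person QALY comparison, and any ANOVA on a cost total with self-reported components, complete-case. These comparisons condition on a post-randomisation outcome that the allocation method is intended to influence.

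Under section 4.1's collection rule and the planned 45% completion, as few as about 84 of 186 would have a full treatment-period record; at 32% dropout, about 126. Both rest on the assumption that questionnaires stop at dropout, on which 3.9 and 4.1 do not agree. The bias in QALYs cannot be sized from the documents. The 0.00125 to 0.020 range shows the mechanism under assumed gains and retention, and its lower end is small.

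The questionnaire-score models, the completion and session analyses, and staff-recorded costs are outside this point. The affected endpoints are secondary, but the cost-effectiveness aim depends on them.

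**What to change.** In section 4:

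1. Limit the no-imputation rule to the mixed models for questionnaire scores.
2. For QALYs and self-reported cost components, use multiple imputation within randomised arm, with baseline values, PHQ-9 scores and sessions completed as predictors, and compare the arms in all randomised participants. Alternatively, derive QALYs as the area under AQoL-8D mixed-model visit means.
3. Analyse staff-recorded assessment, delivery and enrolment costs on all randomised participants.
4. Keep the complete-case analysis, and an analysis that departs from missing at random, as sensitivity analyses.

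Also reconcile 3.9 with 4.1 on whether people who stop the programme are still asked for questionnaires, and 3.9 with 4.3 on when the resource-use questionnaire and TiC-P are given.

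The cost is a few sentences and a modest amount of extra analysis. The main result would rest on a missing-at-random assumption. If dropouts supply no later scores, their values are extrapolated from those who stayed, so collecting data after dropout matters more than the choice of imputation model.
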